In a pilot observational study on 88 patients, median time between first SBT and extubation was 22h with a strategy using SBT-PS and PEEP. We hypothesized that a between-arm difference of at least 24 hours would be clinically relevant to prefer a SBT strategy over one another. With an alpha risk of 5% and a bilateral hypothesis, a power of 80% and a hazard ratio of 2 (based on the ratio of median duration of time between first SBT and successful extubation), a total of 66 successful extubation would be needed. Accounting for both potential deaths before successful weaning and weaning failure (assumed to amount to 30%), we plan to include 94 patients (47 per group).

- 1. STUDY PROCEDURE

|  | Inclusion (day-1) | Day-2 to day-90 | ICU discharge / Death | Day-28 | Day-90 |
| --- | --- | --- | --- | --- | --- |
| Demographic data | X |  |  |  |  |
| Patient weaning readiness | X | X* |  |  |  |
| SBT result | X | X* |  |  |  |
| Arterial blood gas | X | X* |  |  |  |
| *If SBT success* |  |  |  |  |  |
| Cough score | X | X* |  |  |  |
| Abundancy of respiratory secretions | X | X* |  |  |  |
| Extubability criteria | X | X* |  |  |  |
| *If extubation* |  |  |  |  |  |
| Extubation date and time | X** | X** |  |  |  |
| Extubation type (protocolized/self-extubation) | X** | X** |  |  |  |
| Post-extubation NIV characteristics | X** | X** |  |  |  |
| Respiratory physiotherapy characteristics | X*** | X*** |  |  |  |
| High-flow nasal oxygen use | X | X*** |  |  |  |
| Invasive mechanical ventilation status | X | X*** |  |  |  |
| *If reintubation* |  |  |  |  |  |
| Reintubation criteria | X | X |  |  |  |
| *If tracheostomy performed* |  |  |  |  |  |
| Characteristics of tracheostomy |  |  | X |  |  |
| *Follow-up data* |  |  |  |  |  |
| Date/hour of cessation of invasive ventilation and NIV |  |  | X |  |  |
| End of study |  |  |  |  |  |
| Respiratory status |  |  | X | X | X |
| Mortality |  |  | X | X | X |
| *As long as the patient is intubated or tracheostomized  **On the day of extubation and the day after  ***during the 7 days following extubation  NIV denotes non-invasive ventilation, and SBT spontaneous breathing trial. | | | | | |

1. Population of Analysis (intention to treat population)

All subjects who were randomized except patients secondary excluded from the study due to:

- Transfer to another ICU not participating to the study
- Consent withdrawal
- Lack of inclusion criteria or presence of exclusion criteria

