   1. PRIMARY OUTCOME

The primary outcome will be duration (in hours) between study inclusion and successful extubation (defined by the absence of reintubation or death within the 7 days (168 hours) following extubation). Reintubation and resuming of mechanical ventilation for less than 24h related to unplanned surgical procedure will not be considered as extubation failure. Patients extubated but exiting ICU within the 7 days following extubation will be considered as successful extubation. In patients not meeting extubation success criteria, data will be censored at day-90 or date of death whichever comes first.

- 1. SECONDARY PARAMETERS OUTCOMES

1. Rate of first successful extubation: number of patients successfully extubated after their first extubation/total number of patients per group
2. Invasive mechanical ventilation duration (expressed in hours): total cumulative time spent on invasive mechanical ventilation since inclusion per group. Each time period spent on invasive mechanical ventilation from inclusion until successful extubation are summed up. Patients not experiencing successful extubation will be censored at Day 90 or time of death (if earlier than Day 90).
3. Mechanical (invasive and non-invasive) ventilation duration (expressed in hours): total cumulative time spent on invasive and non-invasive mechanical ventilation since inclusion per group.
   - If the patient is successfully extubated with post-extubation NIV: date/time of NIV cessation minus date/time of inclusion. (or date/time of ICU discharge If NIV not ceased at ICU discharge)
   - If the patient is successfully extubated without post-extubation NIV: date/time of successful extubation minus date/time of inclusion.
   - Patients not experiencing successful extubation will be censored at Day 90 or time of death (if earlier than Day 90).
4. Ventilator-free days (VFD) at Day-28 and Day-90. VFD will be computed as follows from the day of inclusion:
   - VFD = 0 if the patient dies between inclusion and day-28 for VFD at day-28, or if the patient dies between inclusion and day-90 for VFD at day-90

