   - VFD = 28-x for VFD at day-28 or VFD = 90-x for VFD at day-90 if the patient is successfully weaned from invasive mechanical ventilation, with x being the number of days from inclusion to last successful extubation. Successful weaning from mechanical ventilation will be defined as extubation without reintubation within at least 7 days (or weaning from mechanical ventilation for at least 7 days for patients with tracheostomy)
   - VFD = 0 if the patient is mechanically ventilated for more than 28 days after inclusion for VFD at day-28, or more than 90 days after inclusion for VFD at day-90
5. ICU stay (days): ICU length of stay between inclusion and ICU discharge
6. Hospital stay (days): hospital length of stay between inclusion and hospital discharge (to home or rehabilitation facility).
7. ICU, day-28, and day-90 mortality: defined as the ratio of the number of death over each period over the total number of patients per group.
8. Reintubation rate: number of patients with any reintubation divided by the number of patients per group

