**DAILY ASSESSMENTS**

These variables will be collected from Day 1 until Day 90:

- If the patient is intubated (SBT data):
  - Preliminary weaning criteria: categorical variable. Present or absent.
  - SBT result: categorical variable. Success or failure.
  - Arterial blood gas in case of SBT success:
    - pH: continuous variable. Expressed without unit, with a precision of 0.01
    - PaCO2: continuous variable. Expressed in mmHg, as an integer
    - PaO2: continuous variable. Expressed in mmHg, as an integer
    - FiO2: continuous variable. Expressed in %, as an integer. For control group, FiO2 is equal to 21+ 3*O2 flow on T-piece
  - Cough score: categorical variable. 0, 1, 2, 3, 4, 5
  - Abundance of respiratory secretions: categorical variable. 0, 1, 2, 3, 4
  - For intervention group: result of SBT-TP, categorical variable. Success or failure.
  - Summary of extubability criteria
    - Acceptable cough (cough score ≥3): categorical variable. Yes or No
    - Acceptable respiratory secretions (abundance of respiratory secretions ≤2): categorical variable. Yes or No
    - No general anaesthesia planned on the next 24h: categorical variable. Yes or No
    - No argument for laryngeal obstruction: categorical variable. Yes or No
    - Number of positive extubability criteria: numerical variable. Ranging from 0 to 4
  - Date (JJ/MM/AAAA)
  - Hour of extubation (HH:MM)
- If the patient is extubated (extubation data):
  - Patient extubated today: categorical variable. Yes or no
  - Extubation type: categorical variable. Programmed extubation per protocol; programmed extubation (protocol violation) or auto-extubation
  - Post-extubation prophylactic NIV (on the day of extubation and the following day): categorical variable. Yes or no
    - In case post-extubation prophylactic NIV:
      - Per-protocol: categorical variable. Yes or no
        - If per protocol, reason(s) for NIV

SBT-TP failure (for intervention group): categorical variable. Yes or no

Age>65 years old: categorical variable. Yes or no

COPD: categorical variable. Yes or no

Chronic heart failure: categorical variable. Yes or no

Chronic respiratory failure: categorical variable. Yes or no

PaCO2>45mmHg at the end of SBT: categorical variable. Yes or no

- - - - - Duration of NIV: continuous variable. Expressed in hours, as an integer
    - In case of no prophylactic NIV:
      - Reason: categorical variable. Per protocol, violation of protocol or contra-indication

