**TERTIARY OUTCOMES**

- Tracheostomy during ICU stay: categorical variable: Yes or no
  - Time of tracheostomy: date variable. Expressed as date (DD/MM/YYYY) and hour (HH:MM)
  - Method of tracheostomy: categorical variable. Percutaneous or surgical
  - Indication(s) for tracheostomy: categorical variable:
    - Difficult weaning: yes or no
    - Swallowing disorder/abundant bronchial secretions: yes or no
    - Other: yes or no
  - Patient successfully weaned from ventilation: yes or no
    - If yes: Time of successful weaning: date variable. Expressed as date (DD/MM/YYYY) and hour (HH:MM)
- End of protocol: categorical variable. Secondary exclusion or end of protocol
  - Date of study end: date variable. Expressed as date (DD/MM/YYYY)
  - In case of secondary exclusion: categorical variable. Transfer to another ICU not participating to the study; Consent withdrawal; In case of serious adverse event, according to the clinician in charge.
  - In case of end of protocol (Cause of end of protocol): categorical variable. No reintubation in the 7 days following extubation; Withdrawing of care or withholding of reintubation decision; ICU discharge ; death ; patient still intubated at Day 90.
- Severe adverse event: categorical variable. Yes or no.
- Respiratory status at ICU discharge (Day 28, Day 90): categorical variable. Not ventilated, non-invasive ventilation (except CPAP), invasive ventilation (tracheostomy), invasive ventilation (intubated), tracheostomy (without ventilation), dead, lost to follow up
- Date of ICU discharge: date variable. Expressed as date (DD/MM/YYYY)
- Date of hospital discharge: date variable. Expressed as date (DD/MM/YYYY)
- Successful extubation: categorical variable. Yes, death or weaning failure
- Successful extubation rank. Discrete variable. NA in case of death
- Time of successful extubation: date variable. Expressed as date (DD/MM/YYYY) and hour (HH:MM).
- Number of reintubation: Discrete variable

1. Statistical Methodology

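### The ventilator-free-day rules give two different scores to a patient reintubated after day 7 and still ventilated at the horizon, and the protocol disagrees with itself on how long ventilation is recorded

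*Protocol*

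**What the plan says.** Section 4.2, item 4, of the protocol has three scoring bullets for VFD.

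- Bullet 1 covers death: "VFD = 0 if the patient dies between inclusion and day-28 for VFD at day-28", and likewise for day 90.
- Bullet 2 gives 28 − x or 90 − x to a patient weaned from invasive ventilation, "with x being the number of days from inclusion to last successful extubation". It also defines success: "Successful weaning from mechanical ventilation will be defined as extubation without reintubation within at least 7 days".
- Bullet 3 covers prolonged ventilation: "VFD = 0 if the patient is mechanically ventilated for more than 28 days after inclusion for VFD at day-28", with the same rule for 90 days.

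Item 8 of the same section defines a further outcome: "Reintubation rate: number of patients with any reintubation divided by the number of patients per group". It sets no time limit after extubation.

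On data collection, the schedule in section 2.6 has a row "Invasive mechanical ventilation status | X | X" whose follow-up entry carries the three-asterisk mark. The footnote ties that mark to the seven days after extubation. In section 4.3, under tertiary outcomes, the causes of end of protocol include "No reintubation in the 7 days following extubation; Withdrawing of care or withholding of reintubation decision; ICU discharge". Under daily assessments, a list that includes reintubation, the same section says "These variables will be collected from Day 1 until Day 90".

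**The concern.** Bullet 2 looks only at whether an extubation held for 7 days. A patient who passes that mark, is reintubated afterwards and is never weaned again keeps the earlier date as x. The later ventilated time is then credited as ventilator-free. Bullet 3 may have been meant to prevent this, but its wording can be taken as a length of ventilation or as being ventilated beyond the horizon. Where bullets 2 and 3 both apply, the text does not say which prevails.

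The second problem is independent of the first. VFD and the rate of any reintubation both need reintubations and re-extubations beyond the seventh day after extubation. Staff who follow the ventilation-status row and treat the end-of-protocol item as the end of daily recording would not look for them. Staff who follow the daily-assessment text would.

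Secondary objective 8 asks whether the assisted strategy raises the reintubation rate, and the trial is open label. These outcomes should not depend on which bullet the analyst applies or which collection instruction the staff follow.

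**Working it through.** The protocol states no numerical figure for VFD, so there is none to reproduce. The sample size in section 2.5 concerns the primary outcome and does not enter here. The check applies the rules to two hypothetical survivors. Their dates are assumptions chosen for illustration.

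- Patient A: extubated D3, reintubated D12, still invasively ventilated at the horizon.
- Patient B: extubated D3, reintubated D12, re-extubated for good on D14.

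In both, the first extubation held for 12 − 3 = 9 days. This exceeds 7, so it counts as successful. For A it remains the last success (x = 3). For B the last success is D14 (x = 14).

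| Reading | A, day 28 | B, day 28 | A, day 90 | B, day 90 |
|---|---|---|---|---|
| Bullet 2 applied, all events recorded | 28 − 3 = 25 | 28 − 14 = 14 | 90 − 3 = 87 | 90 − 14 = 76 |
| Bullet 3 read as still ventilated past the horizon, and prevailing | 0 | 14 | 0 | 76 |
| Nothing recorded beyond 7 days after the first success | 25 | 25 | 87 | 87 |
| Days actually free of invasive ventilation | 12 − 3 = 9 | 9 + (28 − 14) = 23 | 9 | 9 + (90 − 14) = 85 |

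**The rule.** By D28 patient A has spent 3 + (28 − 12) = 19 days on the ventilator. If bullet 3 is a duration counted to D28, it does not reach A, bullet 2 applies and A scores 25. If bullet 3 means still ventilated past D28, A meets both bullets, and 25 and 0 are both defensible from the text. Where bullet 2 is applied, A outranks B by 25 − 14 = 11 days. Where bullet 3 prevails as a status rule, the order is correct.

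**The collection.** The relevant entries, side by side:

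- Pointing to 7 days after extubation, or to ICU discharge: the ventilation-status row (2.6) and the end-of-protocol causes (4.3).
- Pointing to Day 90: the daily-assessment text (4.3), and the reintubation-criteria row (2.6), which has a plain mark under day-2 to day-90 with no footnote.
- Single time points: the date of cessation of ventilation, taken at ICU discharge or death, and respiratory status at ICU discharge, D28 and D90.

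The D28 and D90 status checks would show A as intubated. They would not show B's episode from D12 to D14, because B is off the ventilator at both. If that episode is not picked up elsewhere, B scores 25 where the protocol's own convention gives 14, and B is missing from the count of patients with any reintubation.

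**The case against.** The strongest reply is that bullet 3 already deals with patient A. Read as still ventilated past the horizon, it gives 0 and the ranking is right. That is a natural reading, and on it the inversion disappears. What stands is that the text admits the other reading and gives no precedence. A reader might infer that the protocol certainly ranks a ventilated patient above a weaned one, but the documents do not support that.

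A reader might also infer that the 7-day recording window causes the inversion. It does not. If recording stopped there, B's second extubation would be unseen too, and the two patients would tie at 25. The inversion needs the late events to be recorded, so these are two separate defects.

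On collection, it is fair to say that late reintubations are provided for: the reintubation row carries no 7-day mark and the daily variables run to Day 90. End of protocol also cannot mean the end of all follow-up, since ICU discharge is one of its causes while D28 and D90 status remain scheduled. It would therefore be wrong to say that the schedule omits late reintubation, or that the reintubation rate is cut at 7 days. What stands is an inconsistency that leaves brief late episodes exposed.

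Finally, counting from the last success and giving B no credit for the free days between the two ventilated periods is a stated convention. It is a choice, not an error.

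**Conclusion.** The point holds in two limited parts. First, bullets 2 and 3 of the VFD definition conflict for a survivor reintubated more than 7 days after an extubation and still invasively ventilated at the horizon. In the example the score is 25 or 0 at day 28, and 87 or 0 at day 90. Second, sections 2.6 and 4.3 disagree on how long ventilation is followed, so a late reintubation that resolves between the ICU-discharge, D28 and D90 checks may be lost to VFD and to the reintubation rate.

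The individual scores rest on the assumed dates and on the stated reading of bullet 3. No effect on the group comparison can be given. The protocol reports no frequency of reintubation after day 7 and nothing on whether it would differ by arm. One might infer a bias towards the arm that extubates earlier, because the assisted strategy allows extubation after a failed T-piece trial. The documents do not show this. A shift in arm means would also not be the planned comparison, since section 5.1 specifies the Mann-Whitney test and Hodges-Lehmann differences.

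VFD and the reintubation rate are secondary outcomes. The primary outcome and the sample size are not affected. The point is worth correcting because the scoring is ambiguous and the remedy is cheap.

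**What to change.** In section 4.2, item 4, state that a patient on invasive ventilation at D28 (or D90) scores VFD = 0 for that horizon, and that this overrides bullet 2. Otherwise keep the last-extubation convention. With all dates recorded, A then scores 0 and B scores 14 at day 28, and 0 and 76 at day 90.

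In section 2.6, change the footnote mark on the ventilation-status row. In section 4.3, state that end of protocol does not end this recording. Both should match the Day-90 collection already given under daily assessments, so that the dates of any reintubation and re-extubation are recorded to D90. The existing ICU-discharge, D28 and D90 assessments can be used to obtain them.

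The cost is a few sentences and a few extra dates for the minority reintubated late. No additional visit is needed.

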All the analyses (including primary efficacy analysis) will be performed on this population.

1. Outcome Variables

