   1. GENERAL METHODOLOGY

Quantitative variables will be will be described using the following statistics: number of missing data, mean, standard deviation, quartiles, minimum and maximum values, number and rate of missing variables, and compared between groups with the Mann-Whitney test. No normality check will be performed. Qualitative variables will be reported as absolute and relative frequencies, number and rate of missing variables, and compared between groups with the chi-2 test or the Fisher exact test. Variables will be compared between both groups, except for specific analysis described in 5.2. We will not adjust p-value for multiple comparison. Univariable absolute difference will be reported for each variable as difference [95% confidence interval]. The Hodges-Lehmann method will be used to compute unbiased median differences for outcomes and their CI95%. For qualitative variables, 95% confidence interval will be computed through bootstrapping.

P-value <0,05 with a bilateral hypothesis will be considered as significant. All the analyses will be carried out using R for Windows.

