**HANDLING OF MISSING DATA**

Missing data are reported as NA and will not be imputed. Number of missing observations will be reported in tables. A summary of missing observations will be included in the supplementary material.

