5.2.1.2 Secondary outcomes

Analysis will be carried out as described in 5.1. Results will be reported a table with four columns (intervention group, control group, univariable absolute difference with 95% confidence interval, p-value).

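### ICU and hospital stay have no rule for death, and hospital stay none for patients still in hospital at day 90, so the planned rank comparison is distorted if mortality differs between arms

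*Protocol*

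**What the plan says.** Protocol section 4.2 lists the two stays as secondary outcomes:

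- Item 5: "ICU stay (days): ICU length of stay between inclusion and ICU discharge".
- Item 6: "hospital length of stay between inclusion and hospital discharge (to home or rehabilitation facility" (the parenthesis closes there).

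Neither item mentions death, and item 6 does not mention day 90. The neighbouring items do. Items 2 and 3 (ventilation durations) each carry the rule "Patients not experiencing successful extubation will be censored at Day 90 or time of death (if earlier than Day 90". Item 4 (ventilator-free days) scores death before the horizon as 0.

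For the analysis of secondary outcomes, section 5.2.1.2 says "Analysis will be carried out as described in 5.1". Section 5.1 has quantitative variables summarised "and compared between groups with the Mann-Whitney test", with a Hodges-Lehmann median difference and its 95% confidence interval. On missing values it says "Missing data are reported as NA and will not be imputed". Section 3 defines the analysis set as randomised patients minus listed secondary exclusions and adds "All the analyses (including primary efficacy analysis) will be performed on this population".

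Section 4.3 lists the end-of-stay variable as "Date of hospital discharge: date variable. Expressed as date (DD/MM/YYYY". No discharge destination and no day-90 inpatient status is listed with it.

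**The concern.** A discharge home or to rehabilitation is something that only a patient leaving alive can have. Someone who dies in hospital never reaches the end point of item 6, and item 5 does not say whether death in the ICU counts as leaving it. The analyst must choose, and the obvious choices are both poor:

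- Leave the death without a value. The Mann-Whitney test then compares discharged survivors, a group selected by what happened after randomisation.
- End the stay on the date of death. An early death then ranks as a short, and so favourable, stay.

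This matters because shorter ICU and hospital stays are stated comparative objectives (section 1.2, objectives 5 and 6), each to be reported with a difference, confidence interval and p-value. Lower mortality in the assisted arm is objective 7. A mortality difference, which is the condition under which either choice misleads, is therefore something the trial hopes to find. The trial is open-label, so the rule should be fixed before outcomes by arm are seen.

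**Working it through.** **The plan's own figure.** Section 2.5 sizes only the primary outcome. With a hazard ratio of 2, two-sided alpha of 5%, 80% power and 1:1 allocation, the Schoenfeld formula gives 4 × (1.960 + 0.842)² / (ln 2)² = 4 × 7.85 / 0.480 ≈ 65.4, rounded up to 66 events as stated. Then 66 / (1 − 0.30) = 94.3, against 94 stated. These figures reproduce. No figure is given for either stay.

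**Rules side by side (section 4.2).**

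| Item | Rule for death | Rule for day 90 |
|---|---|---|
| 2, invasive ventilation | censored at death | censored |
| 3, all ventilation | censored at death | censored |
| 4, ventilator-free days | scored 0 | scored 0 if ventilated beyond the horizon |
| 5, ICU stay | none | see fix |
| 6, hospital stay | none | none |

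**How many patients could lack a value.** The documents give no in-hospital mortality rate. If a share d of the 94 die in hospital, or are still inpatients with no later discharge date obtained:

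- d = 10%: 94 × 0.10 = 9.4 without a value, 84.6 left (about 42 per arm)
- d = 20%: 18.8 without a value, 75.2 left (about 38 per arm)
- d = 30%: 28.2 without a value, 65.8 left (about 33 per arm)

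The 30% is an outer illustration. The plan's own 30% allows for patients who die unweaned plus those who fail to wean. It is not a hospital mortality rate.

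**What the unstated rule does to the test.** All inputs other than 47 per arm are assumed. Underlying stay has the same log-normal distribution in both arms (median 25 days, SD 0.7 on the log scale). Death is more likely in sicker patients, who also stay longer. Under the second rule a death occurs at a random 10% to 100% of the underlying stay. There were 4,000 runs, each tested by Mann-Whitney at 5%. Entries are the rejection rate and, where meaningful, the mean difference in medians (intervention minus control).

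| Mortality, control v intervention | Deaths left out | Stay ended at death | Deaths ranked worst |
|---|---|---|---|
| 20% v 20% | 4.9%; −0.1 days | 5.3%; 0.0 days | 4.7% |
| 30% v 15% | 6.6%; +1.4 days | 10.4%; +2.2 days | 16.8% |
| 30% v 10% | 8.6%; +2.1 days | 15.1%; +2.9 days | 24.4% |

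The Monte Carlo standard error near 5% is √(0.05 × 0.95 / 4000) ≈ 0.34 percentage points.

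With equal mortality the choice of rule is harmless. With unequal mortality, the first two rules make the lower-mortality arm look slower to leave hospital, although underlying stay is the same. Ranking deaths worst reverses the direction and favours that arm. Its rejections are not false positives, because the outcome then includes mortality, which does differ. The rule chosen can thus change both significance and sign.

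**The case against.** The strongest reply is that the protocol nowhere says that deaths are dropped. The missing-data rule concerns missing data, and a known death is not obviously that. This stands: a reader might infer that deaths are excluded, but the text supports only that their value is undefined. It does not rescue the outcome, because the other available choice, ending the stay at death, distorted the illustration more.

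Three further inferences are tempting and not supported:

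- *Patients moved to another acute hospital have no value.* The parenthesis in item 6 reads more naturally as saying that such a move does not end the stay. Section 4.3 dates hospital admission from the previous hospital for referred patients, so a stay can span hospitals. Transfers to a non-participating ICU are already outside the section 3 population.
- *Patients in hospital at day 90 have no value.* Section 4.3 puts no day-90 limit on the discharge date. The 90-day study duration in section 2.1 makes a missing date likely, but only if follow-up stops there.
- *Section 3 is contradicted because it promises all randomised patients.* It promises the section 3 population, which already has exclusions.

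It may also be said that handling of deaths in length of stay belongs in a statistical analysis plan, which is not shown. That would hold if the protocol had left the analysis open. Here it fixes the test, the effect measure and the missing-data rule, and gives death rules for the adjacent items. The combination it fixes does not work for these two.

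Finally, these are unpowered secondary outcomes, and with equal mortality no inflation appears. Both statements are correct and limit the weight of the point.

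**Conclusion.** The point holds in a limited form. Items 5 and 6 give no rule for death, and item 6 gives none for patients still in hospital at day 90, unlike items 2 to 4. Under the fixed Mann-Whitney and Hodges-Lehmann comparison without imputation, in-hospital deaths are either left out or counted as favourably short stays. Both distort the comparison if mortality differs between arms.

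The documents do not give the size. The simulated shifts of about 1.4 to 2.9 days rest on assumed mortality of 30% v 15% or 30% v 10%, an assumed distribution of stay, and an assumed link between severity, death and long stay. They show direction and sensitivity and are not a forecast. The primary outcome, its analysis and the sample size are unaffected. The definitions should be corrected, but the point does not threaten the trial's main conclusion.

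**What to change.** For both ICU and hospital stay, in the section 3 analysis population, adopt one of the following:

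1. Analyse time from inclusion to discharge alive, up to day 90, with death as a competing event and censoring at day 90. This is the Fine and Gray method that section 5.2.1.1 already plans for the primary sensitivity analysis.
2. Keep the rank comparison, but give deaths the worst value, as the ventilator-free-day rule does, and rank patients still in hospital (or in the ICU, for item 5) at day 90 next.

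In item 6, add that transfer to another acute hospital does not end the hospital stay. Report length of stay among discharged survivors descriptively, without a p-value.

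Replacing item 6 by days alive and out of hospital is not required. It would change the question in objective 6 and would need inpatient status that is not listed; the day-90 status in section 4.3 is respiratory.

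The cost is small. Two definitions are reworded, and ICU and hospital discharge dates and day-90 mortality are already to be collected. The summary is less familiar than a median length of stay, and a discharge date or day-90 inpatient status must be obtained for a few patients. No sample-size figure changes.
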